#### Secondary outcomes

2.9.2

The secondary outcomes will include composite endpoint events (CCEs), echocardiography indicators (LVEF, left ventricular end diastolic diameter, left ventricular end systolic diameter, A/E), grades of NYHA functional classification, 6MWT results, MLHFQ, TCM syndrome scores. Efficacy assessment of secondary outcomes is based on the change in echocardiography indicators, grades of NYHA functional classification, 6MWT results, MLHFQ, TCM syndrome scores from baseline to 12 weeks and the proportion of patients with composite endpoint events at the end of the trial.

### Safety assessment and adverse events report

2.10

The safety assessment is based on spontaneous reports of adverse events, vital signs, laboratory tests. Vital signs include temperature, blood pressure and heart rate and breathing. Laboratory tests include complete blood count (white blood cell count, red blood cell count, hemoglobin, platelet), routine urine test (urine leukocytes, urine protein, urine latent blood, urine glucose), liver function test (alanine aminotransferase, aspartate transaminase, total bilirubin, r-glutamyl transferase, alkaline phosphatase), renal function test (serum creatinine, blood urea nitrogen), serum electrolytes (serum potassium, serum natrium , serum chlorine ) and 12-lead electrocardiogram.

Adverse events will be recorded at any time during the trial. If any serious adverse event occurs during the trial, the investigator shall immediately take appropriate treatment for the subject, and report to the medical ethics committee of the primary research institution and the sponsor.

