### Objectives

2.1

The main objective of this study is to evaluate the safety and efficacy of SFQX so as to provide high-quality research evidence for its clinical practice compared to placebo for treating CHF.

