### Study procedure

2.4

The participants who provide written informed consent and meet the inclusion and exclusion criteria will be selected at the screening visit, namely visit 1. Eligible participants will be informed via telephone call and will be asked to visit the trial center within 1 week (visit 1). At visit 1, the investigator will record demographic information, other medical history and medication, vital signs, physical examination and so on, and subjects will be randomized to the experimental or control group. The dosage used in this study is 5.4 g (2 bags) of SFQX or placebo 3 times daily for 12 weeks. Tests and assessments will be performed according to the following schedule: Visit 2 (NT-proBNP, echocardiography, NYHA functional classification, 6MWT, Minnesota Living With Heart Failure questionnaire (MLHFQ), TCM syndrome scores, composite endpoint events, complete blood count, routine urine test, liver function test, renal function test, serum electrolytes, 12-lead electrocardiogram); Visit 3 and Visit4 are the same as above. Detailed assessment schedules are outlined in Figure 2.

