### Randomization, blinding

2.6

The central random method is used in this trial where IWRS system is used for central randomization and the assignment scheme is hidden. A block dynamic randomization method is used for randomized allocation. Randomized code generation and drug blinding will be implemented independent of the data. The trial is double-blind where the placebo is the same as SFQX in shape, color, smell, properties, and so on. Both the participants and the investigators will be blinded until completion of the trial.

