### Sample size calculation

2.7

The sample size calculation is based on the proportion of patients with a decrease of NT-proBNP level by at least 30%. According to the reference, 47.95% of the patients in the qili qiangxin capsule group had reductions in NT-proBNP levels by at least 30%, compared with 31.98% of patients in the placebo group.^[13]^ We assume the proportion of patients demonstrating a decrease in NT-proBNP level by at least 30% in the treatment group would be 48%. Therefore, given a type I error rate of α = 0.05, a power of 80% (type II error rate of β = 0.20), the sample size of each group is 146 cases calculated by PASS11 software. Moreover, considering a dropout rate of approximately 20% for randomized patients, a total of 352 patients (experimental group = 176, control group = 176) is required to be randomized for the efficacy analysis.

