### Statistical analysis

2.8

The statistical significance of this study is conducted by 2-sided test and *P* < .05 is considered statistically significant. Statistics software SAS 9.4 will be used for the data analysis. Measurement data are analyzed by paired *t* test, variance analysis, rank sum test, and so on. Enumeration data are analyzed by chi-square test, Fisher exact test, etc. Ranked data are analyzed by Ridit or Cochran-Mantel-Haensel. The analysis data set will be selected from full analysis set, per-protocol set and safety analysis set. Considering the influence of baseline value, covariance analysis or logistic regression analysis will be used to deduct the baseline factor.

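### Adverse events are collected by spontaneous report although safety is part of the main objective, so symptomatic, mainly non-cardiac harms are likely to be under-counted in both arms

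*Protocol article*

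**What the plan says.** Section 2.1 (Objectives) gives safety the same standing as efficacy: "The main objective of this study is to evaluate the safety and efficacy of SFQX".

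Section 2.10 (Safety assessment and adverse events report) names the method: "The safety assessment is based on spontaneous reports of adverse events, vital signs, laboratory tests". The laboratory panels are then itemised, with a 12-lead ECG. The next paragraph adds: "Adverse events will be recorded at any time during the trial".

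Section 2.4 (Study procedure) lists the assessments at visit 2, ending with "serum electrolytes, 12-lead electrocardiogram", and then states: "Visit 3 and Visit4 are the same as above". Composite endpoint events are in that list, and the notes to Figure 2 say that they are also recorded at any time. Section 2.4 refers to Figure 2 for the detailed schedule. The grid of that figure is not available in the text reviewed.

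On blinding, section 2.6 says: "Both the participants and the investigators will be blinded until completion of the trial".

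**The concern.** How an adverse event comes to be recorded affects how many are recorded. Section 2.10 names a passive route: the patient has to bring the problem up. The sentence on recording events at any time fixes when they are written down, not whether anyone asks. This is a stated method, not a detail that the article merely leaves out.

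The other safety measures cover different harms. Blood and urine tests, vital signs and ECG do not detect nausea, diarrhoea, dizziness or rash. The quality-of-life questionnaire and the TCM syndrome score are taken at visits and touch on symptoms, but section 2.9.2 analyses them as efficacy outcomes, so they do not create adverse-event records.

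What is at stake is the harm side of the main objective. If only a share of symptomatic events is volunteered, the reported rates are too low in both arms and the absolute difference is too small. A similar-looking safety table would then be weak evidence that the arms are similar.

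**Working it through.** **The plan's own figure.** The document gives no adverse-event rate and no sample size for safety. Its only sizing figure is for NT-proBNP response (section 2.7): 48% vs 31.98%, alpha 0.05, power 80%, with the two-sided test of section 2.8. The pooled two-proportion formula, with mean proportion (0.48 + 0.3198)/2 = 0.3999, gives

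n = [1.960·√(2·0.3999·0.6001) + 0.842·√(0.48·0.52 + 0.3198·0.6802)]² / (0.48 − 0.3198)² = 145.6, rounded up to 146 per group.

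This matches the stated 146. It is an efficacy figure, and the point here does not depend on it.

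**Inputs for the illustration.**
- From the document: 176 randomised per arm (section 2.7), two-sided 0.05 (section 2.8), both sides blinded (section 2.6).
- Assumed: the true event rates, and a capture share s, meaning the fraction of patients with an event whose event is recorded. Because of blinding, s is taken as equal in the two arms.

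**Effect on the estimates.** With true rates pT and pC, the recorded rates are s·pT and s·pC. The recorded difference is s·(pT − pC), smaller in proportion to s. The recorded ratio is (s·pT)/(s·pC) = pT/pC, unchanged. For 20% vs 10% at s = 0.5, the record shows 10% vs 5%: the difference is halved from 10 to 5 points and the ratio stays at 2.

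**Effect on power.** Power = Φ{[d − 1.960·SE0]/SE1}, where d is the recorded difference, SE0 the pooled and SE1 the unpooled standard error, with 176 per arm. For 20% vs 10%:
- s = 1: d = 0.10, SE0 = 0.0381, SE1 = 0.0377, z = 0.674, power 75%
- s = 0.7: d = 0.07, SE0 = 0.0327, SE1 = 0.0325, z = 0.183, power 57%
- s = 0.5: d = 0.05, SE0 = 0.0281, SE1 = 0.0280, z = −0.180, power 43%
- s = 0.3: d = 0.03, SE0 = 0.0221, SE1 = 0.0220, z = −0.604, power 27%

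Range over other assumed rates:

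| True rates | s = 1 | s = 0.7 | s = 0.5 | s = 0.3 |
|---|---|---|---|---|
| 10% vs 3% | 76% | 60% | 46% | 30% |
| 15% vs 5% | 88% | 73% | 58% | 38% |
| 20% vs 10% | 75% | 57% | 43% | 27% |
| 30% vs 20% | 58% | 41% | 29% | 19% |

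**Events never recorded.** If an event is recorded in none of 176 SFQX patients, the one-sided 95% upper bound on the recorded rate is 1 − 0.05^(1/176) = 1.7%. The bound on the true rate is that figure divided by s: 2.4% at s = 0.7, 3.4% at 0.5 and 5.6% at 0.3.

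The direction is the same in every row. The size is set by the assumptions.

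**The case against.** Five things can be said against the point.

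1. **The visit list proves nothing.** A reader might infer from section 2.4 that nobody asks about adverse events at visits, since the list has no such item. The document does not support that. The list is not exhaustive: it omits vital signs at visits 2 to 4, although section 2.10 makes them a safety measure, and it refers to Figure 2, whose grid is not available. This stands. The point rests on the method named in section 2.10, not on the list.

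2. **The gap is narrower than all symptomatic harm.** Cardiac symptoms are partly covered. Palpitations and breathlessness characterise the syndrome behind the TCM score, and heart rate and ECG are safety items. Worsening-HF hospitalisations, deaths and other serious cardiovascular events are captured as composite endpoint events. This stands, and the point is limited to mainly non-cardiac symptoms.

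3. **The power figures are not a forecast.** Rates and capture shares are assumed, and one open question does not give full capture. It also brings in unrelated complaints. If it added 10 background points to each arm, so that 20% vs 10% became 30% vs 20%, power would be 58%, about the same as at 70% capture without that noise (57%). This stands: a gain in power is not guaranteed. What the question does improve is the completeness of the recorded rates.

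4. **Blinding limits the harm.** Similar capture in the two arms keeps the direction and the relative risk. This also stands. The absolute difference still shrinks, and blinding does not prevent that. Nor does the protocol state a safety test, a margin or a planned claim of no difference, so it cannot be faulted for a wrong safety conclusion.

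5. **An article condenses.** The full protocol or the case record form may specify an enquiry. That is possible, but section 2.10 as published would then describe the method wrongly and still need rewording.

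**Conclusion.** The point holds in limited form. Section 2.10 names spontaneous reporting as the adverse-event method in a trial that makes safety part of its main objective. If this is followed as written, symptomatic, mainly non-cardiac harms are recorded only when volunteered. They are likely to be under-counted in both arms, with a smaller absolute difference and, under blinding, probably the same direction and relative risk. Harms found by laboratory test, vital signs or ECG are not affected.

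The amount cannot be derived from the document. The fall in power from 75% to 57% or 43% is an illustration that assumes true rates of 20% vs 10%, equal capture of 70% or 50% in both arms, and 176 analysed per arm.

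Two stronger readings are not supported: that patients are shown never to be asked, and that the comparison is biased in favour of one arm. This is a change worth making because it is cheap. No stated figure and no primary conclusion depends on it.

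**What to change.** In section 2.10, add that at visits 2, 3 and 4 the blinded investigator asks every patient the same open, non-leading question about new or worse health problems since the last visit. The answers go on the case record form in addition to spontaneous reports, and adverse-event rates are reported by arm from the combined record. Keeping a flag for solicited or spontaneous origin would allow both to be shown.

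If the Figure 2 schedule already includes such an enquiry, reword section 2.10 to match it.

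The cost is one line on the form and about a minute at visits that already take place. The downside is more minor, non-specific events to code in both arms.

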### Data management

2.11

Data collection and management consists of 2 parts: one is Case Record Form (CRF) and another is ResMan public platform in Electronic Data Capture (EDC). Medical information obtained from this trial will be recorded in each patient's CRF and remain confidential which will be checked with the original medical records of the subjects. The researcher's EDC user name and password are specially assigned to enter the data. With the data of each center institution completed and all questions resolved, the project manager and the main researcher need to review the contents of each case again. The data administrator makes a database lock list and saves data management related documents as required. All research data will be kept for 5 years which include confirmation of all subjects, original written informed consent, CRFs, detailed records of drug distribution, etc.

### Monitoring

2.12

A specialized monitor will be responsible for supervising the entire trial process, regularly review and verify whether the trial is conducted and documented on the basis of plan, standard work guidelines, and relevant regulations.

### Ethics and dissemination

2.13

This trial protocol was approved by the Ethics Committee of Xiyuan Hospital of China Academy of Chinese Medical Sciences in 12 December 2019 (2019XLA062-4). Any protocol deviations will be approved by the Ethics Committee of Xiyuan Hospital of China Academy of Chinese Medical Sciences. The trial has been registered with the Chinese Clinical Trial Registry. All participants or authorized surrogates will be given a detailed explanation on this trial with the informed consent form and appropriate time to determine consent or assent.

## Discussion

3

HFrEF is characterized by defects in cardiac contraction. Although the conventional therapeutic approaches in HFrEF management have improved survival rates in patients, the prognosis still remains poor. The efficacy of integrative treatment for CHF with TCM and western medicine has been gradually accredited and the integrative treatment has been considered as an alternative therapeutic strategy for CHF with fewer side effects.^[14]^

As a post-marketed medicine, the composition of SFQX is clear and its quality is assured. Some clinical reports^[15–20]^ have indicated that western medicine combined with SFQX could further improve cardiac function, TCM syndrome, the quality of life and show a clinical curative effect, improve LVEF and narrow left ventricular end diastolic diameter. They may work by reducing plasma brain natriuretic peptide and atrial natriuretic peptide, anti-inflammatory, inhibiting oxidative stress, protecting vascular endothelial function, suppressing rein-angiotensin-aldosterone system system, reversing ventricular remodeling to inhibit myocardial fibrosis. However, there is still a demand on a high-quality and larger-scale clinical research to prove its efficacy and safety in the treatment of CHF.

The study design of this trial has 3 main points.

1.To assess the results of the treatment effectively, a standardized outcome measure is required. We select NT-proBNP as a primary outcome. Plasma will be collected in various hospitals and transported to the central laboratory (the Department of Laboratory Medicine, Xiyuan Hospital of China Academy of Chinese Medical Sciences, Beijing, China) by cold chain for NT-proBNP detection. Plasma NT-proBNP levels were measured by dedicated kit-based NT-proBNP assays (Roche Diagnostics).2.CHF patients with heart-kidney yang deficiency syndrome will be included on the basis of syndrome differentiation and treatment, which reflects both the advantages and characteristics of TCM and the efficacy evaluation of western medicine. Patients with syndrome characterized by palpitations, shortness of breath or wheezing, fear of cold could be diagnosed.3.The study protocol was designed with reference to international clinical trial principles. Three-level quality control measures were taken and data were monitored by EDC system.

Quality control supervisors will ensure that investigators adhere to the study protocol in each center institution. We used the random method of dynamic randomization (multiple blinding) of sub-center group to compete for the group, so as to manage data and reduce deviation in the research. The rigorous design of the trial will ensure an objective and scientific assessment of the efficacy and safety of SFQX in the treatment of CHF.

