### Study design and setting

2.2

This study is designed as a randomized, double-blind, parallel-group, placebo-controlled, multi-center trial. There are 22 institution hospitals located in different areas of China in this trial. A total of 352 stable patients with CHF, who fulfill the inclusion and exclusion criteria, will be randomized into either an experimental or control group in the ratio of 1:1. The general design of this study is demonstrated in Figure 1.

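### Allocation appears to be tied to centre, but the analysis names only the baseline value as an adjustment; if centre is a balancing factor, adding it gives a small, nearly free gain in efficiency

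*Protocol article*

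**What the plan says.** All places are in the protocol article.

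- **Section 2.2 (Study design and setting):** "There are 22 institution hospitals located in different areas of China in this trial". The total is 352 patients, randomized 1:1.
- **Section 2.6 (Randomization, blinding):** allocation is central, through an IWRS. "A block dynamic randomization method is used for randomized allocation". No stratification or balancing factor is named.
- **Section 3 (Discussion):** "We used the random method of dynamic randomization (multiple blinding) of sub-center group to compete for the group". This is the only sentence that connects allocation to centre. It also seems to describe competitive enrolment.
- **Section 2.8 (Statistical analysis):** "Enumeration data are analyzed by chi-square test, Fisher exact test, etc". "Ranked data are analyzed by Ridit or Cochran-Mantel-Haensel", with no stratum named. On adjustment: "Considering the influence of baseline value, covariance analysis or logistic regression analysis will be used to deduct the baseline factor". Centre does not appear in the section.

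**The concern.** Two things do not fit together. First, blocked and dynamic allocation are normally different schemes, so Section 2.6 does not fix one, and only the Discussion suggests that centre plays a part. Second, Section 2.8 goes as far as naming tests and an adjustment variable, but these do not include the factor by which the Discussion says patients are allocated.

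This matters because balancing within centre removes between-centre variation from the true sampling variance of the treatment difference. A test that leaves centre out still counts that variation in its standard error. The standard error is then too wide, the test rejects less often than 5% under the null, and the precision gained by balancing is not used. At stake is a modest amount of power. The validity of a positive result is not in question.

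**Working it through.** **Inputs.** From Section 2.7: response of 48% on treatment; 31.98% on placebo in the cited trial (no separate control assumption is stated); α = 0.05; 80% power; 146 per group; about 20% dropout; 176 randomized per group. From Section 2.8: two-sided testing. From Section 2.2: 22 centres. Assumed, because the documents give no figure: the ICC, meaning the share of outcome variance that lies between centres, at 0, 2%, 5% and 10%.

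**The plan's own figure.** Two proportions, pooled variance under the null, no continuity correction, difference 0.4800 − 0.3198 = 0.1602, mean rate 0.3999:

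n = [1.96 √(2 × 0.3999 × 0.6001) + 0.8416 √(0.48 × 0.52 + 0.3198 × 0.6802)]² / 0.1602² = 145.6, rounded up to 146.

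This reproduces the stated 146 exactly, at 80.1% power. The plan was therefore sized on a comparison without centre.

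**Evaluable number.** 0.8 × 176 = 140.8 per arm, about 141. At that number the null standard error is 0.05838 and the alternative standard error is 0.05760. Power with ICC 0 is Φ[(0.1602 − 1.96 × 0.05838) / 0.05760] = Φ(0.795) = 78.7%.

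**Effect of leaving centre out.** Write f = √(1 − ICC). With 1:1 balance within centre, the true standard error is f times the one used by the unadjusted test. Hence:

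- excess standard error: 1/f − 1
- true type I error, unadjusted: 2[1 − Φ(1.96/f)]
- power, unadjusted: Φ[(0.1602 − 1.96 × 0.05838) / (0.05760 f)] = Φ(0.795/f)
- power, centre-adjusted: Φ[(0.1602 − 1.96 × 0.05838 f) / (0.05760 f)]

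| Assumed ICC | SE too wide by | Type I error, unadjusted | Power, unadjusted | Power, centre-adjusted | Gain (points) |
|---|---|---|---|---|---|
| 0 | 0 | 5.0% | 78.7% | 78.7% | 0 |
| 2% | 1.0% | 4.8% | 78.9% | 79.5% | 0.6 |
| 5% | 2.6% | 4.4% | 79.3% | 80.7% | 1.4 |
| 10% | 5.4% | 3.9% | 79.9% | 82.8% | 2.9 |

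The smaller true variance has to be applied to both power columns. Holding the unadjusted test at its ICC 0 value would overstate the gain.

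**Check by simulation.** 22 centres, 146 per arm, 1:1 within centre, 20,000 runs per setting, plain chi-square against Cochran-Mantel-Haenszel stratified by centre:

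| Assumed ICC | Type I error, chi-square vs stratified | Power, chi-square vs stratified |
|---|---|---|
| 0 | 4.9% vs 5.0% | 80.3% vs 80.4% |
| 2% | 4.6% vs 4.8% | 79.9% vs 80.5% |
| 5% | 4.4% vs 4.9% | 81.1% vs 82.3% |
| 10% | 3.9% vs 5.0% | 81.0% vs 83.7% |

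The direction and size agree with the formulas.

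**Centre size.** 352/22 = 16 randomized per centre on average, and 281.6/22 = about 13 evaluable. Separate terms for 22 centres would be sparse.

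**The case against.** The strongest reply is that silence on centre is not a decision to leave it out. Section 2.8 does not call baseline the only covariate, its lists of tests are open-ended, and centre terms and pooling rules are commonly left to an analysis plan, which is not shown. This stands in part. A reader might infer that the trial ignores centre or adjusts for baseline alone, and the text does not support that. What remains is that the article itself names tests and an adjustment variable that do not match the allocation its Discussion describes, and an analysis plan written from Section 2.8 as it stands would carry the mismatch forward.

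Second, balance within centre is inferred from one unclear sentence, and Section 2.6 names no factor. The two sections need not contradict each other, since each could add a detail to the other. This stands, so the point is conditional on centre being a factor. It is also the reason to ask for one clear description.

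Third, NT-proBNP during the trial is measured in one central laboratory and the endpoint is change within the patient. Both features could keep the ICC low, so the 10% row should be read as an upper illustration and not as an expectation.

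Fourth, plain chi-square is not fixed as the primary responder test, because logistic regression is also named. In logistic regression, adding centre does not shrink the standard error of the log odds ratio; the gain comes from a larger conditional effect. The standard error argument therefore covers the mean difference, the risk difference and the unstratified tests.

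**Conclusion.** The point holds as a conditional one of minor severity: a cheap improvement in clarity and efficiency. If allocation is balanced within centre and centre is prognostic, the methods named in Section 2.8 are mildly conservative. For assumed ICCs of 2% to 10%, about 0.6 to 2.9 points of power are given up relative to an analysis that includes centre; if centre is not prognostic, nothing is lost.

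Two stronger readings should be avoided. A reader might infer that the results would be biased or the test invalid; the error is in the conservative direction, so neither follows. A reader might also infer that leaving centre out pulls power below the planned 80%. It does not: at 146 evaluable per arm the unadjusted test keeps about 80% or more for these ICCs. The 78.7% starting value at about 141 per arm comes from the dropout allowance in Section 2.7 (146 × 1.2 = 175.2, taken to 176, of which 20% are then lost), which is a separate matter. Under these assumptions, centre adjustment would bring that figure back above 80% at an ICC of 5% or more.

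**What to change.** 1. Describe one randomization scheme, with its factors, in the same terms in Sections 2.6 and 3. State plainly whether centre is a stratification or balancing factor.
2. If it is, include centre in the primary analysis in Section 2.8. For the responder endpoint, use a Cochran-Mantel-Haenszel test and risk difference stratified by centre. For log NT-proBNP, use ANCOVA with baseline and a random centre effect.
3. Pool very small centres by a rule fixed before unblinding.
4. If logistic regression is kept for the responder endpoint, include centre there too (for example as a random intercept), and report the result as a conditional effect.

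The cost is wording only: no extra patients, visits or data. The small downside is that, with about 16 patients per centre, pooling or a random effect is needed instead of 22 fixed effects.
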